#### Statistical analyses

The analyses of the clinical efficacy of the treatments are carried out by modeling the primary outcome using mixed linear models (MLM). To compare the efficacy of the two groups, the interaction between treatment condition (TF-DBT vs. S-DBT) or treatment format (online vs. face-to-face) and time is tested for significance. To estimate the effect sizes, standardized mean differences (Cohen’s d) are calculated in TF-DBT before and after therapy as well as between the groups (TF-DBT vs. S-DBT) after therapy.

The main analyses include the evaluation of the ITT sample, which includes all patients who were randomized to a treatment in the study (randomized is analyzed). To analyze the ITT sample, including all participants who had been randomized to the treatment, we will impute missing data by multiple imputation procedures [103]. In addition, the main analyses are performed for all patients who complete the therapy (according to protocol).

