**Aim:**

The primary aim of this study is to investigate the efficacy of this novel DBT adaptation (TF-DBT) compared to standard DBT (S-DBT) as developed by M. Linehan. We hypothesize that TF-DBT is superior to S-DBT on all BPD symptom measures. A second aim of the study is to investigate the efficacy of the delivery format of both treatments (i.e., online vs. face-to-face), with the hypothesis that online therapy is non-inferior to face-to-face treatment.

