## Methods

### Trial design & hypotheses

The study will be conducted by an international research consortium at four different sites: the Central Institute of Mental Health in Mannheim, Germany; the Mental Health Research and Treatment Center at Ruhr University in Bochum, Germany; the Center for Integrative Psychiatry, University of Kiel, Germany; and the Center for Addiction and Mental Health in Toronto, Canada. The study will be conducted between 07/2023 (first patient in) and 03/2026 (last patient out). We aim to include *N* = 260 clients in the trial (*n* = 40 in Mannheim, Germany; *n* = 40 in Bochum, Germany; *n* = 40 in Kiel, Germany; *n* = 20 in Stuttgart, Germany; *n* = 80 in Toronto, Canada; and *n* = 40 German participants with > 1 h travel distance to a research site). Of those, 220 participants will be randomized to receive either TF-DBT or S-DBT in either online or face-to-face formats, resulting in 4 groups (see blue and purple groups in Fig. 1). In addition, 40 participants will be recruited with > 1 h travel distance to one of the research sites. This group will be established to exploratorily investigate potential benefits of the online format for patients who don’t have access to a face-to-face DBT treatment (see the orange group in Fig. 1). Participants in this group will be randomized to receive either TF-DBT or S-DBT in an online-format.

We hypothesize that the TF-DBT groups shows superior improvement in core BPD symptoms (i.e., emotion regulation, self-concept, and interpersonal interaction). We also hypothesize that an online treatment format is non-inferior to a face-to-face format. An overview of the study design is depicted in Fig. 1.

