### Statistical methods

#### Power analysis

The total sample size estimation of *N* = 260 is based on statistical power analyses regarding the intent-to-treat (ITT) sample. In comparing the treatment conditions (TF- DBT vs. S-DBT), a power of 1-*β* = 0.90 is aimed for detecting a minimum clinically relevant difference between the treatment conditions of *d* = 0.43, as recommended in the current Cochrane Review [10]. When comparing the treatment formats (online vs. face-to-face), an equivalence test with a power of 1-*β* = 0.90 is aimed for. The minimum relevant difference is also set at a standardized mean difference (Cohen’s *d*) of 0.43 in accordance with the current Cochrane review and the current Cochrane guidelines [10]. To achieve power, at least *n* = 230 participants are required. Because the psychotherapies investigated each require closed skills groups, participants are randomized into groups of 10. This results in a target number of cases of *N* = 260.

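### Online delivery is hypothesised to be non-inferior and an equivalence test is powered, but the stated analysis is a plain significance test of format by time, which cannot support either claim

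*Protocol article*

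**What the plan says.** The format comparison is described in four places in the protocol article.

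- **Abstract, Aim:** the second aim is introduced "with the hypothesis that online therapy is non-inferior to face-to-face treatment".
- **Methods, Trial design & hypotheses:** "We also hypothesize that an online treatment format is non-inferior to a face-to-face format".
- **Statistical methods, Power analysis:** "When comparing the treatment formats (online vs. face-to-face), an equivalence test with a power of" 0.90 is intended. "The minimum relevant difference is also set at a standardized mean difference" of 0.43, the value used for TF-DBT versus S-DBT. At least 230 participants are said to be needed.
- **Statistical methods, Statistical analyses:** in the mixed linear model, "the interaction between treatment condition (TF-DBT vs. S-DBT) or treatment format (online vs. face-to-face) and time is tested for significance". Condition and format share one sentence and one rule. The effect sizes to be reported "are calculated in TF-DBT before and after therapy as well as between the groups (TF-DBT vs. S-DBT) after therapy"; none is named for online versus face-to-face.

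**The concern.** One question is given three kinds of test: non-inferiority in the hypotheses, equivalence in the power analysis, and a test of difference in the analysis. The first two need a margin. The third has none, and its null hypothesis (no difference in change between formats) is what the investigators hope is close to the truth. Failing to reject it is not evidence for it.

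Followed as written, the second aim would rest on absence of evidence. The 0.43 limit would not enter the decision, and dropout or noisy measurement would make the apparently favourable result more likely. The Background itself records unresolved doubts about the efficacy and safety of remote delivery in patients with high emotional and behavioural dysregulation, so a false conclusion that online is as good would matter.

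**Working it through.** **Inputs from the protocol article**
- Relevant difference 0.43 SD, power 0.90 and required total 230 (Power analysis).
- 220 patients randomised to format (Trial design & hypotheses). The further 40 with long travel distance receive online treatment only.
- Dropout of 39% in the cited online feasibility trial (Background).

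**Assumptions, not stated in the article**
- Two-sided alpha 0.05 (one-sided 0.025 for non-inferiority).
- Equal split of the 220, so 110 per format.
- Independent observations and a simple two-group comparison with SD = 1.
- Missing outcomes of 20% and 39% as illustrations, leaving 88 and 67 per format.

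**Step 1. Reproduce the plan's 230.**
- Superiority, two-sided 0.05, t-test: 114.6, so 115 per arm, 230 in total.
- Non-inferiority, one-sided 0.025, true difference 0: n = 2 × ((1.960 + 1.282)/0.43)² = 113.7, so 114 per arm, 228 in total.
- Equivalence by two one-sided tests at 0.05 each: n = 2 × ((1.645 + 1.645)/0.43)² = 117.1, so 118 per arm, 236 in total.
- Equivalence at 0.025 each: n = 2 × ((1.960 + 1.645)/0.43)² = 140.6, so 141 per arm, 282 in total. This does not match.

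The 230 is matched exactly by superiority and closely by non-inferiority or equivalence at 0.05. The sample-size figure is therefore not the fault.

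**Step 2. Chance of a non-significant result when online is truly worse.** This is 1 minus the power of a two-sided two-sample t-test.

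| True deficit (SD) | 110 per format | 88 per format | 67 per format |
|---|---|---|---|
| 0.43 | 0.112 | 0.190 | 0.305 |
| 0.30 | 0.399 | 0.492 | 0.593 |

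The normal approximation gives 0.110 and 0.298 for the first and last entries of the top row. A non-inferiority test at one-sided 0.025 with margin 0.43 holds the error at a 0.43 deficit to 0.025 in every column.

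**Step 3. The two rules on the same data, 110 per format.**
- SE = √(2/110) = 0.135.
- An estimated deficit is non-significant up to 1.96 × SE = 0.264. At that point the upper 95% limit is 0.264 + 0.264 = 0.53, beyond 0.43.
- Non-inferiority requires an estimate below 0.43 − 0.264 = 0.166.
- Estimates between 0.166 and 0.264 are non-significant yet fail non-inferiority. The chance of landing there is 8% at a true deficit of 0, 28% at 0.20 and 24% at 0.30.

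**Step 4. The converse.** In general a significant deficit can still lie wholly inside a margin. Here that would need 2 × 1.96 × SE below 0.43, that is, an SE below 0.110, which 110 per format does not give in this simple comparison. The practical danger is therefore the non-significant result read as support.

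**The case against.** The strongest reply is that the Statistical analyses section names only the model and the term of interest, while the Power analysis section supplies the type of test and the limit. On that reading 0.43 does govern the decision, and nowhere does the article say that a non-significant interaction will count as support. Equivalence also implies non-inferiority, so powering the stricter test is loose wording and does not undermine the hypothesis. A condensed article may properly leave the confidence-interval rule to a fuller document.

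Part of this stands. The equivalence and non-inferiority wording could be reconciled in a line, and the absence of detail alone would not be a finding. But the analysis section is not silent: it states a significance test for format and applies it in the same words as for the superiority comparison. A fuller plan with a margin-based rule would contradict it.

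The objection is also right about the size of the problem. The 39% is treatment dropout in a study of 39 clients, not outcome loss in this trial. This trial continues assessments after treatment stops, with payment for them at the German sites, and plans multiple imputation. Repeated measures could improve precision and skills-group clustering could worsen it. The missing-data columns are therefore scenarios, not forecasts. The 110-per-format column does not depend on them, and the logic depends on none of the percentages.

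Format is a secondary aim, and the TF-DBT versus S-DBT comparison is unaffected.

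**Conclusion.** The concern holds: the analysis stated for format is wrong for the hypothesis it is meant to test. At the planned size, reading non-significance as support would accept online delivery 11% of the time when it is worse by the plan's own limit, against 2.5% under a proper margin test, and about 40% of the time at a deficit of 0.30 SD. These figures assume two-sided alpha 0.05, 110 per format, independent observations and a two-group comparison in SD units. Other assumptions would change the percentages but not the conclusion. It must be fixed, because as written the trial cannot validly confirm its second hypothesis.

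**What to change.** State one objective for format in the Abstract, hypotheses, Power analysis and Statistical analyses.

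- **If non-inferiority is meant:** declare it when the two-sided 95% confidence interval for the online minus face-to-face difference in BSL-I at 12 months, scored so that higher is worse, lies wholly below 0.43 SD. Take the interval from the primary mixed model, name the SD used for standardising, and require the result in both the ITT and the according-to-protocol sets. Replace the equivalence test in the Power analysis with this test. It needs 228 patients at one-sided 0.025, and 110 per format gives power of 0.89 if the true difference is zero.
- **If equivalence is meant:** use two one-sided tests with limits of ±0.43, state their alpha, and change the hypotheses to match. With 110 per format and a true difference of zero, power is 0.88 at 0.05 each and 0.78 at 0.025 each.

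In either case, take format out of the significance-test sentence, or state that the format-by-time contrast only supplies the interval. Add the format difference and its interval to the reported effect sizes. Say explicitly that 0.43 is the margin, and give a reason for it, since the article presents it as a relevant difference.

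The cost is wording in the analysis and power sections through the article's amendment route, preferably before any comparison by format is seen. No new data are needed, and the planned model already yields the interval.

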## Background

Borderline personality disorder (BPD) is a severe mental disorder characterized by significant instability in affect regulation, self-concept, interpersonal relationships, and behavioral control [1]. It affects approximately 2% of the adult population and is associated with chronic suicidality and recurrent self-harm, leading to significant individual suffering and extensive use of public health resources, particularly emergency and inpatient services [2, 3].

Clinical practice guidelines recommend psychotherapy as the first-line treatment for BPD [4, 5]. Dialectical Behavior Therapy (DBT) has amassed substantial empirical support among evidence-based interventions. Multiple meta-analytic studies have demonstrated its efficacy in improving various BPD-related symptoms, including emotional dysregulation, self-harm, and interpersonal dysfunction [6–9]. The latest Cochrane review, which analyzed 15 randomized controlled trials of DBT, found small to moderate effect sizes for overall BPD severity (*d* = −0.60), self-harm (*d* = −0.28), and psychosocial functioning (*d* = 0.36) compared to treatment as usual [10]. A recent DBT benchmarking study found pre-post effect-sizes of *d* = 0.82 as a DBT effectiveness benchmark, including RCTs and effectiveness studies [11]. While these findings underscore DBT’s effectiveness, they also highlight room for improvement.

Standard-DBT (S-DBT), originally developed by M. Linehan [12, 13], is a comprehensive, multi-component treatment approach. It integrates individual therapy, skills training groups, phone coaching, and therapist consultation teams to enhance patients’ behavioral skills, reduce maladaptive behaviors, increase emotional regulation, improve motivation, and support clinicians in delivering effective therapy. DBT follows a structured treatment hierarchy and operates within a dialectical framework that balances acceptance and change. Linehan’s model divides treatment into four stages, beginning with reducing life-threatening behaviors (Stage I) progressing to the processing of emotional difficulties (Stage II), skill-building in self-esteem and relationships (Stage III), and achieving deeper meaning and fulfillment (Stage IV).

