### Assessments

Data will be collected through clinical interviews and self-assessment questionnaires before treatment and at 3, 6, 9, and 12 months after admission, as well as 6- and 12-months follow-up. The interviews are conducted by blind raters. Additional assessments contain experimental paradigms and ambulatory assessments at pre- and post-treatment (12 months). Furthermore, an electronic daily diary card - a basic tool in DBT – will be used to collect data. An overview of all assessment methods used is illustrated in Figs. 1 and 2. Table 1 depicts a list of all assessment instruments used.

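### The planned Cohen's d values do not match the tested interaction: no pre-post d for S-DBT, no d for online versus face-to-face, and a between-arm d placed after therapy while the test concerns change

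*Protocol article*

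**What the plan says.** Under Statistical analyses, the protocol article models the primary outcome (BSL-I) with mixed linear models. To judge efficacy, "the interaction between treatment condition (TF-DBT vs. S-DBT) or treatment format (online vs. face-to-face) and time is tested for significance". The next sentence turns to effect size: standardised mean differences "are calculated in TF-DBT before and after therapy as well as between the groups (TF-DBT vs. S-DBT) after therapy".

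That sentence names two quantities: a within-arm d for TF-DBT, and a between-arm d for TF-DBT against S-DBT at the end of therapy. It names no within-arm d for S-DBT and no d for online against face-to-face.

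The Power analysis section works on the d scale for both comparisons. It uses 0.43 for the treatment conditions, and for the formats "The minimum relevant difference is also set at a standardized mean difference" of 0.43 as well.

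Assessments are scheduled "before treatment and at 3, 6, 9, and 12 months after admission, as well as 6- and 12-months follow-up", and Table 1 lists the BSL-I at 0 and 12 months. The baseline value needed for either kind of effect size is therefore already part of the schedule.

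**The concern.** There are two separate issues.

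**One arm's change is left out.** A pre-post d in a single arm mixes the treatment effect with time and regression to the mean. It can be read properly only beside the same figure from the randomised control. The article supplies several outside pre-post values: 0.82 (Background), described "as a DBT effectiveness benchmark, including RCTs and effectiveness studies"; 1.35 for DBT-PTSD (rationale section); and 1.13 to 1.44 for online S-DBT (section on access to care). A TF-DBT figure standing alone would be easy to set against those rather than against the trial's own S-DBT arm.

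**The test and the effect size may target different contrasts.** A condition-by-time interaction is about difference in change. A d taken after therapy is, on its face, about difference in level. Readers expect the reported d to be the size of the effect that was tested. If it is a different contrast, the two can point to different conclusions in the same trial. For the formats there is not even a mismatched d to set against 0.43.

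**Working it through.** **The plan's own figure.** With d = 0.43, power 0.90 and two-sided alpha 0.05 (alpha and sidedness are not stated, so this is assumed), the normal approximation gives 114 per arm, 228 in total. The t-test gives 114.6, so 115 per arm and 230 in total. The stated 230 is reproduced, and the sample size is not at issue.

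**Inputs.** N = 260 and d = 0.43 come from the Power analysis section. The rest is assumed: 1:1 allocation (130 per arm), SD = 1 at both times, complete data, and baseline-post correlation r = 0.3, 0.5 or 0.7 (the article gives none). The interaction is read as the difference in change from baseline to 12 months.

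**Chance baseline imbalance, b.**
- N = 260: SD = √(2/130) = 0.124; 95% range ±1.96 × 0.124 = ±0.24 SD. As a share of the target, 0.243/0.43 = 57%.
- N = 220 (the participants randomised between formats, 110 per group assumed): SD = √(2/110) = 0.135; 95% range ±0.26 SD.

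**How a given imbalance moves each estimate.** The post-only contrast shifts by r·b and the change contrast by −(1 − r)·b. The gap between them is r·b + (1 − r)·b = b, whatever r is. At b = 0.243:

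| r | post-only shift | change shift | gap |
|---|---|---|---|
| 0.3 | +0.073 | −0.170 | 0.243 |
| 0.5 | +0.122 | −0.122 | 0.243 |
| 0.7 | +0.170 | −0.073 | 0.243 |

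**Precision at N = 260.** SE is 0.124 for post-only, 0.124·√(2(1 − r)) for change, and 0.124·√(1 − r²) for baseline-adjusted.

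| r | post-only | change | baseline-adjusted | reduction, adjusted vs post-only |
|---|---|---|---|---|
| 0.3 | 0.124 | 0.147 | 0.118 | 1 − √0.91 = 4.6% |
| 0.5 | 0.124 | 0.124 | 0.107 | 1 − √0.75 = 13.4% |
| 0.7 | 0.124 | 0.096 | 0.089 | 1 − √0.51 = 28.6% |

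**How often the two contrasts would disagree.** A normal simulation at true d = 0.43 (400,000 draws per setting) puts the post-only and change contrasts on opposite sides of p = 0.05 in about 16%, 10% and 7% of trials for r = 0.3, 0.5 and 0.7 at N = 260. At N = 220 the figures are about 20%, 14% and 11%.

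**The case against.** The strongest reply is that the article does not say the between-arm d uses raw means. The sentence follows directly on the mixed-model description, and model-estimated, baseline-adjusted means at 12 months would fit its wording. Baseline adjustment and the choice of standardiser are details that an article commonly leaves to the analysis plan. This stands: a reader might infer that the d is raw, ignores baseline and will be the headline result, but the text says none of these. Efficacy is decided by the interaction test.

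A reader might also infer that baseline imbalance distorts the effect size and leaves the test untouched. That is wrong. Imbalance moves both, in opposite directions, and at r = 0.3 it moves the change contrast more. Nor is a post-only d inherently the weaker choice: at r = 0.3 its SE (0.124) is below that of the change contrast (0.147). The precision gain in the table is against a baseline-adjusted estimate, which the article does not say it will test.

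A third inference would be that the plan biases results towards TF-DBT or replaces the randomised control with a historical one. The documents do not support this. A post-treatment d is unbiased under randomisation, the same sentence plans the TF-DBT versus S-DBT comparison, and no benchmark comparison is planned.

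What the reply does not remove is what the article itself fixes: a pre-post d for one arm, a between-arm d placed after therapy beside a test of change, and no d for the formats.

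**Conclusion.** The point holds as a minor improvement to a stated analysis. Two parts rest on the wording alone: the planned effect sizes omit S-DBT's pre-post change, and they omit the format comparison although its relevant difference is set at d = 0.43.

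The third part is conditional. If the between-arm d is a post-only contrast, it differs from the tested change contrast by the full baseline imbalance (SD 0.124, 95% range ±0.24 SD at N = 260). Its SE is then 0.124, where a baseline-adjusted estimate would reach 0.118 to 0.089. The imbalance figures assume 1:1 allocation and equal SDs; the SEs of the change and adjusted estimates also depend on assumed correlations of 0.3 to 0.7. The consequence is loss of coherence and precision, not bias. The stated 230 and the target of 260 are unaffected.

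**What to change.** Reword the effect-size sentence to say that:

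1. pre-post d will be reported for both TF-DBT and S-DBT;
2. the between-arm d and the between-format d, each with a confidence interval, will be derived from the same mixed model's 12-month contrast that is tested;
3. baseline BSL-I will be accounted for in that model, for example by baseline adjustment or by a common baseline mean across groups;
4. the standardiser will be the pooled baseline SD.

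Item 3 also settles how the tested model handles baseline. That is necessary: a baseline-adjusted d placed beside an interaction from a different model would leave the mismatch in place. With a common baseline mean, the group-by-time contrast at 12 months is itself the baseline-adjusted difference, so test and effect size become one quantity.

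The cost is analysis wording only. Baseline and 12-month BSL-I are already scheduled, and no visit, participant or instrument is added. The wording should be fixed before outcome data are examined by arm, so that the estimate is not chosen afterwards.

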#### Discontinuation and dropout policy

Completion according to protocol is defined as participation in at least 30 of the individual therapy sessions over a period of one year. This also applies if participants leave the study early, but at least after 30 sessions. A premature end of therapy is classified according to the following categories:

No-show (discontinuation before the first therapy session, therapy was not started: these patients are not included in the attrition rate); Early dropout (discontinuation within the first four therapy sessions); Withdrawal (if the therapist or treatment team decides that a participant should be withdrawn from treatment); Treatment Dropout (discontinuation of treatment after 5 th therapy session by patient); Research Dropout (participant withdraws consent to participate in the study). Patients who will be no longer available for study-related assessments will be classified as Lost to Follow-Up.

Patients who miss five consecutive weeks of individual therapy or group therapy are considered to have discontinued treatment. These patients are assigned to the dropout category.

Early Remission (Early successful symptom reduction, after 12 sessions at the earliest) is defined as a patient who no longer fulfills the diagnostic criteria for BPD on the IPDE (diagnostic remission assessed by blinded diagnosticians) and has a mean score on the BSL-23 of < 1.07 (this corresponds to no or mild residual symptoms according to Kleindienst et al. [104]) and has achieved all their treatment goals according to their own statement. To classify a participant as early remitted, the patient’s status must be agreed upon by the patient, therapist, and supervisor.

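### The 30-session completer rule has no place for agreed early remission from session 12, so the additional completer analysis can lose some of the best outcomes

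*Protocol article*

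**What the plan says.** In the protocol article, Discontinuation and dropout policy sets the completer rule: "Completion according to protocol is defined as participation in at least 30 of the individual therapy sessions over a period of one year". Its only remark on people who leave early keeps the same threshold: "This also applies if participants leave the study early, but at least after 30 sessions".

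The same section defines a further category: "Early Remission (Early successful symptom reduction, after 12 sessions at the earliest". It requires that the patient "no longer fulfills the diagnostic criteria for BPD on the IPDE (diagnostic remission assessed by blinded diagnosticians", has a BSL-23 mean below 1.07, and "has achieved all their treatment goals according to their own statement". Patient, therapist and supervisor must agree on the status. No sentence says whether such a patient counts as a completer, and early remission is not in the list of categories for a premature end of therapy.

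Statistical analyses then uses the completer definition: "In addition, the main analyses are performed for all patients who complete the therapy (according to protocol". The ITT evaluation comes first: "The main analyses include the evaluation of the ITT sample, which includes all patients who were randomized to a treatment in the study".

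**The concern.** Two rules in one section collide. Early remission is a course that the protocol itself foresees, yet a patient who follows it and stops at sessions 12 to 29 does not meet the protocol's definition of completion.

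The exclusion depends on outcome. Early remission requires a low BSL-23, and the Primary outcome section reports a correlation of 0.83 between the BSL-23 and the BSL-I, the primary outcome. Leaving these patients out therefore comes close to selecting on the endpoint.

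The label is at stake too. Read literally, a patient who stops after the fifth session fits the treatment-dropout category, and five consecutive missed weeks also lead to a dropout classification. The best responders could thus be reported as attrition.

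**Working it through.** **1. Setting the rules side by side**

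| Sessions attended when therapy ends in agreed early remission | Early remission possible? | Meets the completer rule? |
|---|---|---|
| fewer than 12 | no | no |
| 12 to 29 | yes | no |
| 30 or more | yes | yes |

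Only the middle row is affected. The TF-DBT phases add up to 20 + 15 + 8 + 2 = 45 sessions, so the threshold is 30/45 = 67% of the planned course.

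**2. The plan's own figure**

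The power analysis asks for at least 230 participants for d = 0.43 at 90% power. Alpha is not stated; I assume two-sided 0.05.

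- Normal approximation: n per arm = 2 × (1.960 + 1.282)² / 0.43² = 113.7, so 114 per arm and 228 in total.
- t-test version: 114.6, so 115 per arm and 230 in total.

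The figure reproduces. It is sized on the ITT sample, so the completer rule does not touch it.

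**3. Illustration of size (assumed rates)**

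The article gives no early-remission rates, so every rate below is an assumption. Take a normal 12-month outcome with SD 1 and a true difference of 0.43. A share p of an arm is removed, selected on a latent remission score that correlates ρ with outcome. The mean of those left worsens by

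m(p) = ρ × φ(z_p) / (1 − p).

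With ρ = 0.5:

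- p = 5%: 0.5 × 0.1031 / 0.95 = 0.054
- p = 10%: 0.5 × 0.1755 / 0.90 = 0.098
- p = 20%: 0.5 × 0.2800 / 0.80 = 0.175

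The completer difference is 0.43 − [m(p in TF-DBT) − m(p in S-DBT)]. Dividing by the reduced SD in the remaining set gives the completer d.

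| TF-DBT vs S-DBT removed | Raw difference | Completer d | Shift in d |
|---|---|---|---|
| 10% vs 10% | 0.43 | 0.45 | +0.02 |
| 10% vs 5% | 0.387 | 0.40 | −0.03 |
| 20% vs 5% | 0.309 | 0.32 | −0.11 |
| 5% vs 10% | 0.473 | 0.49 | +0.06 |

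The last row shows that the sign reverses if early remission is more common in S-DBT.

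A second model applies one common outcome threshold for remission in both arms. Removing 5.8% vs 2.3% gives a completer d of 0.39, and 20.5% vs 10.5% gives 0.34: shifts of 0.04 to 0.09 on the d scale. In raw units these shifts are about 0.07 to 0.15 SD, because the SD of the remaining set shrinks as well.

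A tighter link between remission and outcome gives more. With 20% vs 5%, d falls to 0.28 at ρ = 0.7 and to about 0.22 at ρ = 1. The range of 0.03 to 0.11 therefore belongs to the moderate scenarios and is not an upper bound.

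**4. Pre-post effect among completers**

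This is understated even with equal rates. With ρ = 0.5, and if baseline severity is unrelated to remission, mean improvement in the arm falls by m(p): 0.05 SD at 5% and 0.10 SD at 10%.

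**The case against.** The strongest reply is that the text never says that early remission ends therapy or that remitters are not completers. Early remission has its own paragraph, apart from the dropout list, and the authors may mean to count such patients as completers. That stands as a limit on certainty. It does not remove the point: the article states the completer rule without exception, and repeats the 30-session condition for those who leave early.

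A reader might infer that the rule is biased against TF-DBT because that treatment aims to accelerate change. The documents do not support this. By the article's own phase lengths, sessions 1 to 20 are preparation and 21 to 35 are exposure. Session 30 thus falls inside the exposure phase, before the phase on building a life worth living. The condensing it describes is coverage of all stages within one year, not an end before session 30. More early remission in S-DBT is as plausible.

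A reader might also put the loss at a quarter to a third of the target effect. Rates of 15% vs 5% and a gap of 1.0 to 1.5 SD give (0.15 − 0.05) × 1.0 to 1.5 = 0.10 to 0.15 SD, or 23 to 35% of 0.43. The arithmetic is correct, but the rates and the gap are invented, and most of the moderate scenarios give a smaller shift in d.

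Nor do the documents give a reason why early remission should differ between online and face-to-face delivery. Treatment is crossed with format, so a treatment effect on remission would act in both formats.

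Finally, a 30-session threshold is a legitimate exposure-based definition, and adding early remitters admits patients below it only if they did well. That is true and is the real cost of the change. It does not defeat it, because agreed early remission is a course that the protocol provides for, and the strict set can be shown beside the extended one.

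**Conclusion.** The point holds as a defect in the definition of the completer set. As written, agreed early remission at sessions 12 to 29 falls outside that set and could be reported as dropout. It rests on the natural, though unstated, reading that therapy ends at early remission.

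The completer pre-post improvement is understated if any such patients exist. The between-arm completer contrast is biased only if early-remission rates differ by arm. The direction is unknown. Under moderate assumed rates the shift in d is roughly 0.03 to 0.11. With equal rates the raw difference is unchanged, and d rises slightly because the SD shrinks.

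The criteria are demanding, so the patients concerned may be few. It would be wrong to conclude that the trial's main result is at risk: ITT keeps every randomised patient, and the sample size rests on ITT. This is a cheap improvement to a supplementary analysis.

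**What to change.** Define the according-to-protocol set as at least 30 individual sessions or classified early remission, and use the scheduled BSL-I assessments of early remitters as observed. Report the number of early remitters by arm and by format, separately from dropouts. Keep the strict 30-session set as a sensitivity analysis.

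The cost is one clause in the completer definition and one extra analysis run. The downside is that the extended set admits some patients with fewer than 30 sessions on the basis of their outcome; the strict set beside it shows openly how much that matters. The clause should be fixed before outcome data are analysed, since a later decision on who is a completer would be informed by outcome. The change is analytic only and leaves the clinical remission rule as it stands.
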